# Efficacy of dopamine, epinephrine and blood transfusion for treatment of fluid refractory shock in children with severe acute malnutrition or severe underweight and cholera or other dehydrating diarrhoeas: protocol for a randomised controlled clinical trial

**DOI:** 10.1136/bmjopen-2022-068660

**Published:** 2023-04-11

**Keywords:** Paediatric intensive & critical care, Paediatric gastroenterology, Respiratory infections

## Abstract

**Introduction:**

Diarrhoea is one of the leading causes of under-5 childhood mortality and accounts for 8% of 5.4 million global under-5 deaths. In severely malnourished children, diarrhoea progresses to shock, where the risk of mortality is even higher. At icddr, b Dhaka Hospital, the fatality rate is as high as 69% in children with severe malnutrition and fluid refractory septic shock. To date, no study has evaluated systematically the effects of inotrope or vasopressor or blood transfusion in children with dehydrating diarrhoea (eg, in cholera) and severe acute malnutrition (SAM) or severe underweight who are in shock and unresponsive to WHO-recommended fluid therapy. To reduce the mortality of severely malnourished children presenting with diarrhoea and fluid refractory shock, we aim to compare the efficacy of blood transfusion, dopamine and epinephrine in fluid refractory shock in children who do not respond to WHO-recommended fluid resuscitation.

**Methods and analysis:**

In this randomised, three-arm, controlled, non-masked clinical trial in children 1–59 months old with SAM or severe underweight and fluid refractory shock, we will compare the efficacy of dopamine or epinephrine administration versus blood transfusion in children who failed to respond to WHO-recommended fluid resuscitation. The primary outcome variable is the case fatality rate. The effect of the intervention will be assessed by performing an intention-to-treat analysis. Recruitment and data collection began in July 2021 and are now ongoing. Results are expected by May 2023.

**Ethics and dissemination:**

This study has been approved by the icddr, b Institutional Review Board. We adhere to the ‘Declaration of Helsinki’ (2000), guidelines for Good Clinical Practice. Before enrolment, we collect signed informed consent from the parents or caregivers of the children. We will publish the results in a peer-reviewed journal and will arrange a dissemination seminar.

**Trial registration number:**

NCT04750070.

STRENGTHS AND LIMITATIONS OF THIS STUDYThis study includes severely malnourished children with diarrhoea having fluid refractory shock.This study evaluates the cardiac function of the study children at the bedside by point-of-care cardiac ultrasound.This study is excluding children Down’s syndrome or any chronic illness.Evaluation of non-diarrhoeal children having shock is out of scope for this study.

## Introduction

### Background and rationale

Diarrhoeal diseases are the second-leading cause of death in under-5 children and were responsible for the deaths of 370 000 children in 2019.^1^ In Bangladesh, diarrhoea causes 7.3% of under-5 deaths in 2019.^2^ Children with severe acute malnutrition (SAM) frequently present with diarrhoea, and fluid refractory shock is one of the common complications of diarrhoea.^3^ The management of these children is challenging. There is a lack of evidence-based guidelines for the management of fluid refractory shock in severely malnourished children. Optimised management of the altered haemodynamics in fluid refractory shock is yet to be explored and different opinions exist among experts, especially for malnourished children. Data from the Dhaka Hospital of icddr, b demonstrates that despite appropriate care, 69% of children having comorbidities such as severe malnutrition die from fluid refractory shock.^4^

The WHO recommends the administration of isotonic saline boluses in a dose of 15 mL/kg over 1 hour (maximum two times), followed by blood transfusion in a dose of 10 mL/kg over 3 hours in cases unresponsive to isotonic fluid boluses.^5^ If blood pressure does not restore to the desired level after fluid bolus, the condition is termed as a fluid refractory/septic shock. Quick arrangement of safe blood is difficult, especially in resource-poor settings. The Fluid Expansion As Supportive Therapy (FEAST) trial showed significantly higher mortality associated with the administration of saline bolus or albumin^6^ in children having severe sepsis. Inotropes such as dopamine perform better than excessive fluid administration^7^ when myocardial dysfunction or vasoregulatory failure results in shock rather than absolute hypovolaemia.^7 8^ Recent studies also demonstrated that epinephrine resulted in the early resolution of shock with survival benefits than dopamine.^9 10^ It is a complex situation whether to use blood or inotropes in fluid refractory shock. Severely malnourished children are in reductive adaptation with different haemodynamics than well-nourished children. Despite the very high death rates, the management of fluid refractory shock in severely malnourished children with early inotropes or vasopressors has never been studied.

Malnourished children have less left ventricular mass^11 12^ as well as left ventricular function as evidenced by echocardiography,^11 13^ which may constitute a bad prognostic parameter. The FEAST trial reported that in the bolus group, a significantly higher proportion had a terminal event cardiac rather than respiratory or neurological.^14^ Point-of-care (POC) cardiac ultrasound is an emerging tool to assess cardiac function and fluid responsiveness in shock and it is non-invasive. Using the POC ultrasound to differentiate hypovolaemic shock from distributive shock, for example, fluid refractory/septic shock, measuring ventricular function and inferior vena cava (IVC) collapsibility can reduce the diagnostic time and increase the accuracy of diagnosis.^15 16^ Usually, in hypovolaemic shock, both end-diastolic and end-systolic volumes are reduced,^16^ left ventricle (LV) is small having a hyperdynamic wall motion.^17^ Whereas in fluid refractory/septic shock, LV is hyperdynamic^17^ and only end-systolic volume is reduced.^16^ Again, the diameter of the IVC at inspiration and expiration and their ratio provides useful information regarding fluid responsiveness.^16^ To date, no study has evaluated systematically the effects of vasopressor and inotrope(s) in children with dehydrating diarrhoea (eg, in cholera) and SAM having fluid refractory shock unresponsive to conventional WHO-recommended fluid therapy.

The proposed study will provide valuable data to determine whether resuscitation strategies including vasopressor and inotropes or blood result in increased survival in children who are severely malnourished with fluid refractory shock and diarrhoea. In addition, POC cardiac ultrasound will provide information on whether the shock resulted from a fluid deficit or cardiac dysfunction.

### Objective

The study aims to compare the efficacy of blood transfusion, dopamine and epinephrine in fluid refractory shock in children having SAM or severe underweight who do not respond to WHO-recommended fluid resuscitation.

### Trial design

This is a randomised, three-arm, controlled, non-masked clinical trial in children 1–59 months old with SAM or severely underweight and shock (figure 1). With parental written informed consent, children are allocated to the study interventions following randomisation, in addition to usual supportive care that includes broad-spectrum antibiotics, oxygen inhalation, intravenous glucose, etc. The study protocol follows the Standard Protocol Items: Recommendations for Interventional Trials guidance for protocol reporting (modified to reflect the ongoing study activities)^18^ (table 1).

**Figure 1 F1:**
[figure not shown]
Study flow chart showing the procedures of screening and enrolment and allocation of a child in any of the three treatment categories and ways of rescue therapy if the study goal is not achieved. Hb, haemoglobin: WAZ, weight for age.

**Table 1 T1:** Standard Protocol Items: Recommendation for Interventional Trials (SPIRIT) Figure. The schedule of enrolment, interventions, and assessments.

Indicators	Screening	Study period						
		Enrolment and allocation	Study drugs administration and F-U	Rescue therapy	Hosp course up to disposal	Follow-up after discharge		
						1st follow-up	2nd follow-up	28th follow-up (over phone)
Time point	Day 0	Hour 0	Hour 0–3 (1 hour for dopamine and epinephrine, 3 hours for Blood)	Hour 1—disposal (for dopamine and epinephrine) Hour 3—disposal (for blood)		Day 7±2	Day 21±2	Day 28±3
Enrolment:								
Eligibility screen	x							
Informed consent	x	x						
Randomisation and allocation		x	X					
Interventions:								
Different drugs (dopamine or epinephrine or blood)			X					
Assessments:								
Demographic		x						
Comorbidities		x						
Physical examination	x	x	X	x	x	x	x	–
Primary outcome:								
Case fatality								x
Secondary outcomes:								
Treatment failure			X					
MAP stabilisation at 48 hours after enrolment				x	x			
Mechanical ventilation			X	x	x			
Incidence of heart failure			X	x	x			
Duration of ICU stay					x			
Duration of total hospitalisation					x			
Time-to-achieve recovery from shock			X	x	x			
Ventricular function by cardiac USG	x	x		x	x (If require)			
IVC collapsibility	x	x		x	x (If require)			
*Detection of leptin from stored blood		x						

*According to the addendum (ERC approval on 21 October 2021), at the end of the study, stored blood samples will be tested for leptin.

F-U, follow-up; ICU, intensive care unit; IVC, inferior vena cava; MAP, mean arterial pressure; USG, ultrasonography.

## Methods

### Participants and interventions and outcomes

#### Study setting

The study is being conducted at the Dhaka Hospital of the icddr, b, Dhaka, Bangladesh. icddr, b is the largest diarrhoeal diseases hospital in the world. Annually a total of 194 838 patients of all ages and genders got treatment and care from icddr, b, and 57.2% were under 5 years of age. In addition to diarrhoeal illness, many patients have other health conditions, such as pneumonia, malnutrition, sepsis and electrolyte abnormalities. For critically ill patients, there is an intensive care unit (ICU) facility present within the hospital, equipped with contemporary life support measures, including mechanical ventilators, bubble continuous positive airway pressure (BCPAP) oxygen therapy, high-flow nasal cannula oxygen therapy and syringe pumps for vasopressor support. The ICU of the Dhaka Hospital of icddr, b manages around 1000 paediatric patients each year. More than 80% of them have a poor socioeconomic background. About one-third have severe malnutrition, and one-fourth of them have severe sepsis or fluid refractory shock, there are other different wards for the treatment of diarrhoeal illness, respiratory problems and malnutrition. icddr, b possesses a well-equipped laboratory service capable of performing a range of clinical tests proposed in this study.

##### Inclusion criteria

Inclusion criteria are children aged 1–59 months of either sex having diarrhoea and SAM who develop fluid refractory shock either at admission or at any point during their treatment in the hospital (which might be due to cholera or other dehydrating diarrhoea or severe sepsis). We also included children having severe underweight as they are also vulnerable and their mortality rate is also high. We are using corrected weight for the anticipated loss of fluids to calculate SAM or severe underweight.

##### Exclusion criteria

Exclusion criteria are severe anaemia (haemoglobin (Hb) <5 g/dL) and sclerema where blood transfusion is a mandate, congenital anomalies (tetralogy of Fallot, TOF)/atrial or ventricular septal defect (trisomy 21, etc), negative blood groups, a requirement of cardiopulmonary resuscitation during screening and non-consent from the caregivers/parents.

##### Randomisation

The permuted block randomisation technique is followed to select treatment arms for each child. The randomisation procedure was planned and executed by a scientist from icddr, b who is not involved in the study. The randomisation list containing the subject identification numbers (IDs) and the corresponding group allocation remained concealed. IDs are chronologically assigned to each new study participant. After randomisation, an opaque envelope containing the name of the allocated intervention group is opened.

##### Study duration

Twenty-four months.

### Collection of baseline information

Any SAM children with fluid refractory shock, either at admission or developed at some point during their treatment period, within the defined age group are screened for study eligibility criteria by the study physician. According to the inclusion and exclusion criteria, parents or attending caregivers of those eligible children are invited for providing consent for their children to be enrolled in the study. A signed written informed consent form by parents or caregivers gives data concerning the study, attainable advantages and risks, and voluntary nature of participation, as well as the right to cancel the child’s participation in the study at any time (even after giving the initial consent) while not providing any reason; after this, children are enrolled by the study physician. One copy of the signed consent document was given to the caregiver of every participant and another copy was reserved for the study documentation. A pretested case record form is used to collect relevant medical history information, including the nature and duration of illness, medication for current illness and any history of significant past illness including pneumonia and diarrhoea. The form is also used to collect information on sociodemographic characteristics, such as age, sex, religion, gestational age, parental age with education and occupations, source of drinking water and sanitation, type of fuel use, cooking place and smoking history, average monthly income of the family, number of siblings, and number of rooms in the home.

Information is also collected about each child’s feeding practice, which included their history of breastfeeding, formula feedings, or alternative complementary feedings, and also immunisation status. Data on clinical examination findings are recorded by the study physician and include pulse, respiratory rate, axillary temperature, anthropometric measurements (ie, height, weight, mid-upper arm circumference (MUAC) for calculation of Z score), chest auscultation, oxygen saturation, presence or absence of chest wall indrawing, cyanosis and mental status (ie, normal, irritable or lethargic) and response (according to alert, response to voice or pain, unconscious (AVPU) scale). Each child’s weight is measured by using an electronic weighing scale with a precision of 0.1 kg; length is measured using a standard-length board with a precision of 0.5 cm and MUAC is measured using a standard MUAC tape with a precision of 0.2 cm by the trained and experienced study nurse of Dhaka hospital. Fever is defined when the axillary temperature is 38°C or greater. Respiratory rate is counted for a full 60 s by exposing the trunk when the child is awake and calm; the presence of lower-chest-wall indrawing is noted at the same time. Oxygen saturation is measured using a portable pulse oximeter (Handheld Vital Signs Monitors-NT1D, Solaris Medical Technology, USA) with a probe on a finger or toe when the child breathes in room air. Oxygen saturation of <90% is defined as hypoxaemia, which is an indication for supplemental oxygen therapy by using BCPAP. Blood group and Rh typing are done at the bedside and we exclude the child having negative blood groups.

Bedside Hb (if not known) is checked by using HemoCue Hb 301 analyser (HemoCue AB, Sweden) during the screening period to exclude severely anaemic children requiring an urgent blood transfusion. The length of ICU stays, the total length of hospitalisation and time-to-achieve-recovery (time required for the restoration of mean arterial pressure (MAP) after the starting of the intervention for fluid refractory shock) are recorded. We are also keeping a record of stool and urine volume. Any deterioration or adverse events (ie, signs of heart failure or need for mechanical ventilation) are also documented. Both the study and outcome are recorded including treatment failure/success, hospital discharge, referrals and deaths or left against medical advice.

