Children with fluid refractory shock are randomised to blood transfusion, dopamine or epinephrine therapy. Children in the dopamine arm (treatment category A) receive dopamine, 8 μg/kg/min (increasing the dose after 15 min to 12 μg/kg/min to a maximum of 15 μg/kg/min, up to the achievement of goal). Children in the epinephrine arm (treatment category B) receive epinephrine, 0.1 μg/kg/min (increasing the dose after 15 min to 0.2 μg/kg/min to a maximum of 0.3 μg/kg/min, up to the achievement of goal). We are using peripheral lines to give dopamine or epinephrine. Drugs are prepared as intravenous infusion and instilled by an infusion/syringe pump. Children in the blood transfusion arm (treatment category C) receive a transfusion of whole human blood at a dose of 10 mL/kg over 3 hours (figure 1). To arrange blood within the time frame, we have an institutional volunteer donor list, two medical technologists dedicatedly work for this study, and we are also excluding children having negative blood groups. Even after that, If blood could not be arranged within 1 hour after the event of fluid refractory shock, we will start rescue therapy considering the event as treatment failure. In addition to the study interventions, broad-spectrum antibiotic therapy, oxygen therapy and frequent monitoring, all children receive intravenous maintenance fluids with half-strength normal saline and 5% dextrose @ of 3 mL per kg per hour during the arrangement of blood transfusion and intervention with inotropes. Along with maintenance fluid, we add intravenous fluid if diarrhoea continues or a child develops dehydration. Intravenous fluid maintenance is continued for 6 hours after the achievement of a goal and is further continued if the goal is not achieved. Our goal is to achieve MAP>50 mm Hg and/or urine output ≥1 mL/kg per hour. After randomisation, we monitor children at every 15 min interval during the intervention to assess mental status by using AVPU, an acronym from ‘alert, verbal, pain, unresponsive’, capillary refill time, rate and volume of the radial pulse, cold/warm extremities, urine output, blood pressure, respiratory rate, peripheral capillary O_2_ saturation and features of heart failure. We measure BP manually using the standard cuff. To minimise the use of a catheter, we apply a paediatric urine collector bag and measure the urine output. However, for a female child, it is difficult to measure. We are considering an indwelling catheter if required. Mechanical ventilation is provided if the child did not respond to bubble CPAP (if SpO2<85% at least after an hour of bubble CPAP oxygen therapy) or had a respiratory failure (pH<7.2 and Partial pressure of carbon dioxide (PCO_2_)>60 mm Hg in ABG analysis or Oxygen saturation to fraction of inspired oxygen ratio (SpO_2_/FiO_2_)<265). Children who develop complications such as acute abdomen not responding to conservative management or acute renal insufficiency requiring dialysis are referred to a suitable higher facility for proper management. At the achievement of the goal, we continue the dose of dopamine or epinephrine for 6 hours. We follow up with the child every 30 min to 1-hour interval. Thereafter, we reduce the dose in a stepwise manner similar to how we increased the dose. If the child becomes hypotensive again, we reintroduce the previous dose and follow the same procedure for further iteration.

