#### Reporting of adverse events

Serious adverse events (deaths) after initiation of the study intervention are recorded and presented to the DSMB within 24 hours of the event. The report includes a detailed clinical history, the study intervention and management given until the outcome. We contacted over the phone for study participants who were referred.

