## Ethics

This study has been approved by the institutional review board (IRB) of the icddr, b (Protocol No. PR#20021, version 2.2, dated 21 July 2022). We are conducting the study in compliance with the ‘Declaration of Helsinki’ (2000), Guideline for Good Clinical Practice. Before enrolment, we collect signed informed consent from the parents or caregivers of the children. We are strictly maintaining privacy, anonymity and confidentiality of data or information identifying the patients or caregivers. Participants’ medical information, particulars of treatment and laboratory test results will be kept confidential and under lock and key; only the research staff will have access to this information. The risk to enrolled subjects from participation in the study is minimal. Adverse medical events are anticipated as the study is enrolling critically ill patients. This protocol has been reviewed and approved by the DSMB of icddr, b. DSMB is a five-membered board that independently reviews the activity of the study. We are reporting the occurrence of any serious adverse event (eg, death) to the DSMB within 24 hours of the event and will follow their recommendations. There is no influence of the funder at any stage of the research, starting from study design and up to publication. Study patients are recruited into three different groups. For this clinical trial, injection epinephrine and injection dopamine are being used in fluid refractory shock. These drugs are already in use in the ICU of Dhaka hospital of icddr, b.^22^ WHO recommends blood transfusion, and we are routinely practising it. Regardless of the study result, finally, it will be disseminated.

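### The stated adverse event rule is closed to heart failure and ventilation, so harms particular to a peripheral vasoactive infusion or to transfusion are not assured a systematic record by arm

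*Protocol article*

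**What the plan says.** Three places in the protocol article describe the recording or reporting of harms.

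- Collection of baseline information: "Any deterioration or adverse events (ie, signs of heart failure or need for mechanical ventilation) are also documented".
- Reporting of adverse events, where the scope is narrower still: "Serious adverse events (deaths) after initiation of the study intervention are recorded and presented to the DSMB within 24 hours of the event".
- Ethics: "We are reporting the occurrence of any serious adverse event (eg, death) to the DSMB within 24 hours of the event".

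Outcome measures makes 28-day case fatality primary and lists ventilation and heart failure among the secondary outcomes. The only harm rows in the schedule (Table 1) are those same three items.

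On exposure, Study intervention and procedure says "We are using peripheral lines to give dopamine or epinephrine", with the dose continued for 6 hours after the goal is reached. Children in the third arm "receive a transfusion of whole human blood at a dose of 10 mL/kg over 3 hours". Under Rescue therapy, children who fail in the dopamine or blood arm go on to epinephrine.

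On monitoring, the same section says "After randomisation, we monitor children at every 15 min interval during the intervention to assess mental status by using AVPU", together with "capillary refill time, rate and volume of the radial pulse, cold/warm extremities, urine output, blood pressure, respiratory rate", oxygen saturation and features of heart failure.

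**The concern.** The adverse events that are named do not match the treatments being compared. Heart failure is the harm one expects from giving volume. Ventilation captures respiratory deterioration from any cause. Neither is specific to a vasoactive infusion through a peripheral line, and neither would pick out a transfusion reaction that did not progress to one of them.

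The trial is non-masked and is meant to inform whether inotropes or blood should be used in fluid refractory shock. If the stated rule is followed, an arm could be reported without infusion-site, ischaemic, arrhythmic or transfusion-reaction events either because there were none or because nobody was asked to write them down. A reader of the results could not tell which.

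**Working it through.** **1. Is the list closed, or is this loose wording?** In the same section of the article, *ie* introduces complete lists on two other occasions: the anthropometric measurements, and the categories of mental status. Where examples are meant the article writes *eg*, as for cholera in the Introduction and for death in Ethics. Read consistently, the parenthesis is a definition. It also attaches to the whole phrase, including the deterioration that the sentence mentions first.

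**2. The three statements side by side.**

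| Section | Scope as written |
|---|---|
| Collection of baseline information | Adverse events are heart failure signs or need for ventilation |
| Reporting of adverse events | Serious adverse events are deaths |
| Ethics | Any serious adverse event, death being an example |

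The second and third describe the same 24-hour reporting to the DSMB with different scope. The third would cover a serious ischaemic injury, arrhythmia or transfusion reaction. None of the three assures a record of a non-serious one.

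**3. Does the bedside monitoring fill the gap?** Only in part. Capillary refill, pulse and cold extremities are checked in all arms, but the operational definition of septic shock uses the same signs. A poor reading therefore does not separate a drug effect from the disease. The monitoring list has no infusion-site, rhythm or transfusion-reaction item.

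**4. How many children are exposed.** The plan's sample size reproduces. With fatality 0.61 against 0.31, two-sided alpha 0.05 (sidedness is not stated, so this is assumed), 80% power and unpooled variance:

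n = (1.960 + 0.842)² × (0.61×0.39 + 0.31×0.69) / 0.30² = 39.4, so 40 per arm.

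Then 40 / 0.90 = 44.4, so 45 per arm, and 3 × 45 = 135. Two arms are allocated a vasoactive infusion: 2 × 45 = 90 of 135, or 67%. Rescue epinephrine in the blood arm adds to this.

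**5. What recording could show.** The documents give no event rates, so the rates r below are assumptions. The chance of at least one event among n children is 1 − (1 − r)ⁿ.

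| True rate r | n = 45 (one arm) | n = 90 (both drug arms) |
|---|---|---|
| 2% | 60% | 84% |
| 5% | 90% | 99% |
| 10% | 99% | over 99.9% |

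A harm of 5% or more would very probably be seen in an arm if someone recorded it.

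**6. What recording could not show.** With no events in 45, the one-sided 95% upper limit is 1 − 0.05^(1/45) = 6.4%. The upper end of a two-sided 95% interval is 1 − 0.025^(1/45) = 7.9%. For a formal contrast of one arm against another with no events, a two-sided Fisher test gives p = 0.056 at 5 of 45 and p = 0.026 at 6 of 45, so 6 events are needed. The chance of 6 or more among 45 is about 2% at a true rate of 5% and 29% at 10%. The gain from recording is description, not a powered comparison.

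**The case against.** The strongest reply is that the article condenses a fuller protocol (version 2.2), and that neither that protocol nor the case record form is shown. The form may carry more than the article says, and an itemised adverse event list is the kind of detail an article leaves out. This stands as a limit: nothing can be asserted about the form itself. It does not remove the point, because the article is not silent. It states a definition, and the definition is narrow.

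A reader might infer that such harms leave no record at all. The documents do not support that. Vital signs and perfusion are checked every 15 minutes during the intervention, lactate and cardiac ultrasound are repeated at 4–6 hours, acute kidney injury has its own operational definition, and referrals are recorded. Serious events may also reach the DSMB under the Ethics wording. Circulatory overload after transfusion would probably appear as heart failure.

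A reader might also infer that the arms' safety cannot be compared. That too goes further than the documents allow: 28-day death, heart failure and ventilation are all outcomes available by arm. Nor does the article plan any claim that a drug is as safe as blood; its stated objective is efficacy.

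Two practical objections also stand. The monitoring list contains no rhythm check, so a requirement to look for arrhythmia would add a procedure. A transfusion reaction can occur only where blood is given, so that item offers no real contrast between arms.

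**Conclusion.** The concern holds in a limited form. As stated, documented adverse events are closed to two items that are already secondary outcomes, and the article disagrees with itself on whether serious adverse events extend beyond death. Harms particular to a peripheral dopamine or epinephrine infusion, or to transfusion, are not assured a systematic record by arm, so their absence from an arm could not be interpreted.

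The gap touches 90 of 135 children by allocation on the infusion side and 45 on the transfusion side. Common harms would be visible if recorded (90% chance of at least one case in 45 at an assumed 5%); rarer ones could only be bounded, at about 6.4% when none is seen. The efficacy analysis and the sample size are unaffected. The conclusion rests on reading *ie* literally, as the article uses it elsewhere, and on the article's wording reflecting what is done. If the case record form already lists these events, only the wording needs correcting. It is worth fixing because the remedy is small, but it does not threaten the primary result.

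**What to change.** - In Collection of baseline information, replace the closed parenthesis with an open one (*including*).
- Add a short checklist to the existing monitoring sheet in all three arms: infusion-site injury or limb ischaemia; arrhythmia if seen in usual ICU monitoring, so that no procedure is added; transfusion reaction where blood is given; heart failure; ventilation. For each, record onset time and whether it arose on allocated or rescue treatment.
- Tabulate the events descriptively by randomised arm with 95% CIs, without a claim of comparative safety.
- Reconcile Collection of baseline information, Reporting of adverse events and Ethics, so that they agree on what is recorded and what is reported to the DSMB.

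The cost is a few tick boxes, a little more to look for at checks already made, and one table. No dose or treatment rule changes. There are three downsides. Children already enrolled need a chart look-back or are reported as not assessed; at the August 2022 status that is 18, leaving 135 − 18 = 117 for prospective capture, and the number will since have moved. Site findings are partly subjective and would be made unblinded. With 45 per arm, most of these harms can only be described.
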